### 8.3. Follow up Assessments (D14, D30, Months 3, 6, 12)

Survival at D14 is the primary end point of this trial, and defined as survival until 23.59 on Day 14. Follow up assessments will be conducted on D14 and D30 and at 3, 6 and 12 months. Patients who have been discharged before these dates will be issued a mobile telephone for the purposes of follow-up. Patients will be invited to return to the treatment centre for the D14 and D30 visits and then subsequent follow up will occur by phone or at a treatment centre. When patients are not able or willing to attend a follow-up visit on D14 and D30 at the treatment centre, field workers will follow up by phone. Remaining follow up visits will be arranged at a survivor's clinic or suitable local health facility. An outreach team may attempt to visit participants who are unable to attend a clinic or cannot be reached by phone, if it is considered safe and feasible to do so. Reasonable expenses for travel and loss of earnings will be paid at these follow up visits.

Patient status on follow-up assessment days will be collected (admitted, met discharge criteria, deceased). In addition, visits at D30 and months 3, 6, and 12 will seek information on symptoms post recovery. Trial staff will notify appropriate healthcare providers if the patient reports new symptoms that require further clinical assessment.

Primary/secondary outcome data for these visits can be collected at any point after the respective days.

### 8.4. Procedures for provision of TKM

Patients randomized into the treatment cohort will receive TKM-130803 in addition to the supportive therapy provided to all patients.

TKM-130803 will be administered at a dose of 0.3mg/kg by IV infusion at a rate of **1.25 mL/min** administered over approximately 120 minutes in a total volume of 150ml. Infusions should be administered using an infusion pump, to ensure a well-controlled rate of infusion.

For full details of infusion preparation and administration please refer to the trial Standard Operating Procedure for drug administration.

Doses will be administered once daily, for seven days. In the event of suspected drug-related toxicity or a change in the patient's clinical condition, the dose of TKM-130803 may be reduced to a minimum of **0.24 mg/kg** once daily at the discretion of the treating physician. If the infusion is interrupted and resumed, the total infusion should be completed within 4 hours of infusate preparation. The patient will be in recumbent position for dose administration.

There are two potential adverse outcomes that require close clinical supervision.

1. Infusion related reactions may occur following commencement of the infusion. As the drug is given once a day, the timing of administration will be set to coincide with the presence of the trial staff in the treatment area. This will allow monitoring of symptoms and a decision to slow or halt the infusion if

necessary. Pre-medication such as paracetamol may be given. IM adrenalin will also be made available for the event of an anaphylactic reaction.

2. Cytokine release syndrome may occur several hours after the infusion commences. Health care workers involved in care of patients receiving TKM will receive additional training to recognise the constellation of symptoms that are associated with it (flushing, headache, fever, hypotension, chills, nausea and vomiting). Management of a cytokine related event will prioritise immediate care (i.e. stopping of infusion (if ongoing), provision of IV fluids) and prompt medical review of the infusion speed and dose. Additional drugs (including steroids) may be given to ameliorate symptoms, at the treating physician's discretion. Procedures for safety reporting are outlined in 11.2.

### **8.5. Laboratory Samples**

All patients, both in the observational and TKM cohort, will have regular blood samples drawn and analysis performed; see Section 9.2 Laboratory Assessments. Also, any residual volumes will be stored. Those in the observational cohort will have all the laboratory tests as for those in the TKM cohort; malaria, pregnancy (for women of childbearing age), ebola testing, electrolyte, renal and hepatic function testing. However, they will not have PK samples taken; these will only be taken from patients receiving the trial drug.

### **8.6. Procedures for standard care**

The supportive therapy received by patients will not be affected by participation, or non-participation, in the trial. All patients will receive standard supportive therapy and for those patients in the study, this will be recorded. Treatment provided by clinical staff is based on the ETC guidelines for management of EVD. This includes oral and/or intravenous fluid, resuscitation, empirical antibiotics, antimalarial agents, and also symptom control, which includes antiemetics, antipyretics/analgesics, and anti-diarrhoeal agents, as appropriate to the patient's symptoms.

### **8.7. Treatment Interruption**

In the event of a SUSAR or other significant treatment related event, the treating physicians will determine if study treatment will continue on the basis of clinical picture and severity and resolution of the event. Consultation with the Independent Data Monitoring Committee will be made in the case of uncertainty to determine if the treatment should be discontinued.

If there is an indication of a cytokine response in the safety cohort (first 4 patients) then recruitment will be reviewed. The IDMC will review data from the complete cohort prior to recruitment being opened to all suitable patients. The safety cohort may be expanded following advice from the IDMC.

### **8.8. Discontinuation of Trial Treatment**

Each participant has the right to discontinue use of study treatment at any time. In addition, the Investigator may discontinue treatment at any time if the Investigator considers it necessary for any reason including:

- Ineligibility (either arising during the trial or retrospectively having been overlooked at screening)
- An adverse event which requires discontinuation of the trial medication

- Disease progression which requires discontinuation of the trial medication
- Patient or physician decision

The reason for any discontinuation of treatment will be recorded in the case record form.

### **8.9. Withdrawal from the Study**

Patients, or parents/guardians/representatives when they have given consent on behalf of the patient, are free to withdraw consent and stop study participation at any time for any reason. In this case, the patient's clinical management will continue to be provided according to standard care and will not be affected by the decision to withdraw. Outcome data and the reason for withdrawal will be recorded when possible. Data collected up to the date of withdrawal will be used in study analysis.

## **9. DATA COLLECTION**

### **9.1. Clinical data acquisition**

Study dosing, sampling and data collection will begin after enrolment. Figure 3 shows the clinical data acquisition schedule.

Patient demographic data and medical history will be collected for all patients at the time of enrolment in the trial. While a participant is an inpatient, information will be collected daily on signs and symptoms, medications and blood products received, and the results of non-trial blood samples. For patients who are receiving TKM that day, detailed records of physiological monitoring and adverse event monitoring (outlined in section 8.2) will be provided.

SD1 (Study Day 1) is defined as the first day these data are collected. For patients who are in the TKM cohort this is likely to be the same day the first dose is administered.

These data will be collected daily for participating patients up to D14, or discharge, or death, whichever occurs first. Patients who achieve discharge criteria before D14 will stop the inpatient testing schedule upon discharge.

For patients not enrolled in the study, only anonymous survival data will be collected.

Discharge criteria are:

- 72 hours without fever or significant symptoms AND
- A significant improvement in clinical condition AND
- Able to feed, wash and walk independently AND
- Ebolavirus RNA PCR test negative

Figure 3: Clinical data acquisition procedures

[figure not shown]

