| Secondary | 
TKM
 
1. To evaluate the impact of TKM-130803 treatment for adults on:
 
a) Overall mortality at D14
 
b) Time to recovery
 
c) Late mortality
 
d) Viral load
 
e) EVD symptoms
 
f) EVD antibody response
 
g) Long term clinical recovery
 
2. i) To assess the safety of TKM treatment for adults.
 
ii) To measure the pharmacokinetics (PK) of TKM following repeat dosing
 
Observational
 
To characterise the natural history of EVD in an ETC.
 
a) Time to recovery
 
b) Late mortality
 
c) Viral load
 
d) EVD symptoms
 
e) EVD antibody response
 
f) Long term clinical recovery
 | 
TKM
 
1. a) D14 mortality in all patients allocated to TKM-130803 treatment (not excluding deaths in first 48 hours).
 
b) Time to meeting ETC discharge criteria.
 
c) Mortality at D30 and months 3,6,12 after first dose of study treatment
 
d) Viral load
 
e) Presence and duration of symptoms (SDs 1-14)
 
f) Anti-Ebolavirus IgG titre (recruitment and D30)titre
 
g) Clinical assessment at D30 and months 3, 6, 12.
 
2. Incidence of SARs, key adverse events (SDs 1-14) and monitoring of vital signs (pulse rate, blood pressure, respiratory rate, temperature) pre, during and at 0, 1, 2, 4 and 8 hours post end of infusion
 
ii) PK pre-dose and at the end of infusion on SDs 1, 3, 5 and 7
 
Observational
 
a) Time to meeting ETC discharge criteria.
 
b) Mortality at D30 and months 3,6,12 after admission
 
c) Viral load
 
d) Presence and duration of symptoms (SDs 1-14)
 
e) Anti-Ebolavirus IgG titre (recruitment and D30)titre
 
f) Clinical assessment at D30 and months 3, 6, 12.
 |

Note that there are two counting systems for days in the trial: days from admission (prefixed with D) and study days (prefixed with SD) from time of first data collection (see section 9.1).

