#### From within this cohort, additional inclusion criteria for randomization to the TKM cohort (stage 2):

- Not pregnant (although this might change after TSC review of the first 15 patients)
- Not breastfeeding (for lactating women)
- Agrees to use birth-control for 3 months post study.

The study of TKM treatment will concern the outcomes of all patients who are allocated to TKM treatment. For these patients, D1 will be the day of admission to the treatment centre. The primary response for the trial will be survival to D14 (yes or no). Patients who are allocated to TKM treatment and survive the first 48 hours after admission but do not actually receive it or who fail to complete the course of therapy, for any reason, will nevertheless be included in this primary analysis.

The observational study will include those considered eligible for TKM treatment but who are not allocated to it due to the limited number of available treatment beds or those patients otherwise eligible for the

study but do not comply with stage 2 of the eligibility criteria, up to the maximum number of available observational beds. For the analysis of the outcomes of these patients, D1 will be the day of admission to the treatment centre.

Data from participants who for any reason are ineligible for the trial or refuse to participate will be included (anonymously) in the primary analysis of the observational group. All patient outcome data is routinely recorded in all ETCs and shared anonymously with WHO, therefore the use of anonymised D14 outcome data is in line with current practices.

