### **8.2. In-patient Days**

Standard safety assessments of patients will include daily monitoring of vital signs (pulse rate, blood pressure, respiratory rate, temperature), symptoms and SARs whilst they remain in the ETC. Any non-study medication received will also be recorded.

In addition, for the TKM treatment cohort, vital signs and assessment of possible infusion related reactions will be assessed at the following approximate time points: pre-infusion, during the infusion (preferably between 30-90 minutes), at the end of infusion (0 hour), and at 1, 2, 4 and 8 hours post end of infusion, as well as at additional time points if indicated by the patient's clinical condition.

The recruitment process for the safety cohort is described in Section 7.4. The IDMC will review data from the safety cohort prior to recruitment being opened to all eligible patients. The safety cohort may be expanded following advice from the IDMC.

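### Section 9.1 ends daily collection at D14, but the symptom and key adverse-event outcomes run over SD1–14, and section 8.2 sets no day limit for in-patients

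*Supplement*

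**What the plan says.** All references are to protocol v2.9.

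- **Two clocks.** The note under the table in section 6 separates "days from admission (prefixed with D) and study days (prefixed with SD) from time of first data collection". Section 7.5 fixes the first clock for patients allocated to TKM: "For these patients, D1 will be the day of admission to the treatment centre". It sets the same origin for the observational patients. Section 9.1 fixes the second: "SD1 (Study Day 1) is defined as the first day these data are collected".
- **Outcome windows.** Section 6 lists "Presence and duration of symptoms (SDs 1-14") as a secondary outcome in both cohorts, and "Incidence of SARs, key adverse events (SDs 1-14") as the safety outcome in the TKM cohort.
- **End of daily collection.** Section 9.1: "These data will be collected daily for participating patients up to D14, or discharge, or death, whichever occurs first". Its next sentence, on patients who meet the discharge criteria early, also uses D14.
- **In-patient monitoring.** Section 8.2 asks for daily vital signs, "symptoms and SARs whilst they remain in the ETC", with no day limit.
- **Enrolment lag.** Sections 8.1 and 15.2 allow consent up to 48 hours after a patient arrives with a confirmed diagnosis, or up to 48 hours after the patient is told of a positive PCR result obtained in the centre. Under section 9.1 data collection begins only after enrolment.

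**The concern.** The two outcomes are defined on the study-day clock and the collection stop on the admission clock. The clocks agree only when SD1 is the day of admission. Otherwise SD14 falls after D14, and a site that follows 9.1 stops recording before the outcome window closes, while a site that follows 8.2 carries on.

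The patients concerned are those still in the centre after D14, that is, the slow recoverers. If 9.1 is followed, their symptom duration is cut at a study day that depends on how long enrolment took, and the cut is related to the outcome being measured. If sites read the protocol differently, the length of the window could also vary by site. At stake is the completeness of two secondary outcomes, one of them part of the safety assessment.

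**Working it through.** The plan gives no figure to reproduce. The check is calendar arithmetic.

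**Inputs**
- D1 is the day of admission (section 7.5).
- SD1 is the first day of data collection, after enrolment (section 9.1). Write SD1 = Dk.
- The outcome window is SD1 to SD14, 14 days (section 6).
- Daily collection stops at D14 if the patient is then alive and not discharged (section 9.1).
- For a patient who arrives with a confirmed diagnosis, consent may come up to 48 hours after arrival (section 8.1). Taking first collection to fall within that window, k is 1, 2 or 3.
- For a patient confirmed after admission, the 48 hours run from the PCR result. The documents give no upper limit for the time from admission to that result, so k of 4 or more is an assumption.

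**Formulas**
- SD14 = D(k + 13).
- D14 = SD(14 − k + 1) = SD(15 − k), the last study day covered under 9.1.
- Days lost = 14 − (15 − k) = k − 1.

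**Results for a patient still admitted through SD14**

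| SD1 | SD14 falls on | Covered under 9.1 | Days lost | Share of 14 |
|---|---|---|---|---|
| D1 | D14 | SD1–14 | 0 | 0% |
| D2 | D15 | SD1–13 | 1 | 7.1% |
| D3 | D16 | SD1–12 | 2 | 14.3% |
| D4 (assumed late PCR) | D17 | SD1–11 | 3 | 21.4% |
| D5 (assumed late PCR) | D18 | SD1–10 | 4 | 28.6% |
| D7 (assumed late PCR) | D20 | SD1–8 | 6 | 42.9% |

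**Who is affected.** Two conditions must both hold: SD1 is later than D1, and the patient is still in the centre after D14. A patient who leaves or dies by D14 stops for that reason, and the D14 limit removes nothing. A patient who leaves between D14 and SD14 loses fewer days than the table shows. The documents do not say how many patients would meet both conditions.

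**The same patient under section 8.2.** Monitoring continues to the end of the stay, so no day up to SD14 is lost. The two sections therefore give different answers for the same patient on the days from D15 to SD14.

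**After the change.** With a stop at SD14, days lost to the rule are 14 − 14 = 0 for any k. SD14 is never earlier than D14, so nothing now collected would be dropped.

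**The case against.** A reader might infer that the last days of the window go uncollected in every patient whose SD1 falls after admission. The documents do not support that. Section 8.2 continues daily monitoring for the whole stay, and an earlier sentence of section 9.1 also ties daily collection to being an in-patient. This part of the objection stands: loss of data is not established, only that the protocol gives conflicting instructions. It does not remove the conflict. Section 9.1 is the data-collection section and its stop is explicit, whereas section 8.2 speaks of monitoring and does not say that the study record continues.

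A reader might also infer that safety follow-up as a whole is cut short. For SARs that is not so: section 11.2 has sites report them within 48 hours, with no D14 limit. For key adverse events the effect is less direct than for symptoms. Section 11 has them entered on the case report form when new or worsening, again without a D14 stop, and the adverse-event monitoring named in section 9.1 is tied to days on which TKM is given. Even so, several of the listed events are symptoms that the daily record would capture, so the stop still bears on how fully they are seen.

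Two further points are fair. Figure 3, the acquisition schedule, cannot be seen in the text available and may state the window differently. And the follow-up visits do ask about symptoms, but only from D30 and only about symptoms after recovery, so they do not replace daily data.

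**Conclusion.** The point holds as an inconsistency among sections 6, 8.2 and 9.1. Whenever SD1 falls after D1, section 9.1 closes daily collection before the SD1–14 window ends, while section 8.2 points the other way.

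For patients still admitted through SD14, following 9.1 loses 1 of 14 days when SD1 is D2 and 2 of 14 when SD1 is D3. These two figures rest on first collection falling within the 48-hour window after arrival. Larger losses need PCR confirmation that came later after admission, which is an assumption.

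The consequence is limited. Patients discharged or dead by D14 are untouched by the rule, and the number affected cannot be derived from the documents. Survival to D14 and the stopping rule both run on the admission clock and are unaffected. This is a small correction worth making, not a threat to the trial's conclusion.

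**What to change.** 1. In section 9.1, and in Figure 3 if it repeats the rule, end daily collection at SD14, discharge or death, taking the earliest of these.
2. Change the following sentence of section 9.1, on patients who meet discharge criteria before D14, to the same clock.
3. State in section 8.2 that daily study recording for the SD1–14 outcomes runs at least to SD14 while the patient is in the centre. Changing 9.1 alone would not make it agree with 8.2, which covers the whole stay.
4. Keep D14 for vital status, so that the primary endpoint and the stopping rule stay as they are.

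The cost is a short wording amendment and one to a few extra days of recording for in-patients whom section 8.2 already has monitored daily. Days after discharge would still not be recorded daily.

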## 9.2. Laboratory Assessments

The timing of laboratory sampling for research purposes is outlined in Figure 4. The 'recruitment' time point for laboratory samples is defined as after consent is signed and screening completed but before first dose. This could be 1 calendar day before first dose, or be same day (SD1).

The only essential blood tests are the diagnostic EBOV positive PCR on admission and EBOV negative PCR prior to discharge (a single, or two negative PCR results will be acceptable, depending on local ETC policy). Adult and pediatric samples will be reduced in volume according to standard procedures such that no patient will have more than 0.6 ml/kg (>1% blood volume) taken on any one day, nor more than 2.4 ml/kg (approximately 3% of blood volume) taken in any four week period. Standard care samples will be prioritised over research samples if volume reduction is required. Ability to take samples is dependent on

staff availability, the availability of suitable laboratory facilities, caseload and, particularly at discharge once patients are released to go home, the willingness of the patient. Research samples and standard care samples may be reduced where required, to maintain care standards and staff safety, and reflect the assays that can be performed by the laboratory attached to the ETC. Study samples may also be reduced if the patient refuses them or is not available. Other chemical or biological assays may be performed using the same blood volumes if available and useful to inform patient safety or study outcomes.

Figure 4: Sample scheduling for trial specimens – TKM study.

[figure not shown]

\* Timing assumes that patients commence infusion on day 1, following the recruitment day. If commencement of infusion occurs at a later time, the schedule will be altered to reflect this.

^ 1 x 4 mL EDTA sample is obtained for PCR and malaria. An additional 1 x 4 mL EDTA sample will be obtained on study days when FBC is required. Patients who have PK testing undertaken will have 2 x EDTA samples drawn

Depending on laboratory capacity, it may not be possible to perform the following tests or complete assays. Where possible, tested parameters may include:

Biochemistry: Renal profile (sodium, potassium, chloride, blood urea nitrogen, creatinine), Bone profile (calcium, magnesium), liver function tests (ALT, AST, alkaline phosphatase, total bilirubin, albumin, total protein), other ( C-reactive protein, total carbon dioxide, glucose, total creatinine kinase, CK-MB)

Coagulation studies: prothrombin time, activated partial thromboplastin time, and international normalised ratio

Full blood count: haemoglobin, total white cell count, platelet count, lymphocyte count, granulocyte (neutrophil) count, monocyte count, haematocrit, mean corpuscular volume

The same sampling schedule applies to all patients irrespective of their allocation in either the observational or TKM cohort, with the exception of pharmacokinetic drug testing. This will only be performed on patients receiving the trial drug.

**Malaria testing:** Malaria diagnostic tests will be performed on the triage blood sample as part of standard care. The results of these tests will be recorded. Trial staff will only request a malaria test at recruitment if it has not been done by the clinical treating staff at triage.

**Pregnancy testing:** For women of childbearing age (15-49 years) a chromatographic  $\beta$ HCG test will be performed on the triage blood sample. Urine testing is also acceptable.

**Ebolavirus testing:** Patients will have blood samples collected at triage for EVD diagnosis by PCR and prior to discharge to confirm clearance of viral RNA, both as standard care. In addition, a study only EDTA will

be taken daily for the first 7 days of study involvement (SDs 1-7) and on SD30 for PCR. The PCR result for all samples will be shared with the clinical team in real time. Samples obtained for PCR are typically  $\leq 4$  ml whole blood in an EDTA tube; finger or heel-pricks of blood on a dry swab are sometimes obtained when venepuncture is not possible. Ebolavirus RNA will be detected by PCR, as per local clinical laboratory protocols. Additionally, plasma anti-Ebolavirus antibody titres will be determined by analysis performed by partner laboratories of residual volumes obtained at recruitment and SD30.. This is to determine whether the treatment influences the subsequent production of specific antibodies.

**Biochemistry:** A 4ml sample will be drawn for additional testing on recruitment, SDs 2, 4 and 7, discharge and 30 to investigate electrolytes, renal, metabolic and hepatic function. Electrolyte disturbances are a common complication of Ebola. Results from toxicological studies indicate TKM may cause hepatic impairment, although this has not been shown in human trials. This information will be provided to clinical staff in real time.

**Heamatology (Full blood count and differential white cell count):** A 4ml EDTA sample will be drawn for additional testing on recruitment, SDs 2, 4, 7 and SD30 to measure wherever possible haemoglobin, total white cell count, platelet count, lymphocyte count, granulocyte (neutrophil) count, monocyte count, haematocrit and mean corpuscular volume (indicated as FBC in Figure 4).

**Pharmacokinetic testing.** Pharmacokinetic (PK) testing will only be undertaken on patients receiving the study drug. In order to assess the PK of TKM following repeat dosing, it is recommended that blood samples be obtained for PK analysis, if feasible, depending on the capabilities of the ETC, the availability of appropriate laboratory facilities and the clinical condition of the treated individual. It is recommended that PK samples (each one 4ml EDTA tube) be obtained pre-dose and again at the end of the infusion, on SDs 1, 3, 5, and 7 of treatment. The PK samples should be obtained, processed and stored according to the instructions provided separately in the laboratory manual.

**Peripheral blood mononuclear cell (PBMC).** If it is possible for the laboratory to perform PBMC separation and store separated PBMCs appropriately, then a proportion of EDTA blood will be used for this purpose. Separated PBMCs may be used subsequently for cytokines mRNA analysis, B cell repertoire sequencing, or any other type of genetic analysis based on the outcome of infection.

**Residual volumes.** Residual volumes of all samples will be stored and subsequently shipped to international partner laboratories for confirmatory testing and quantification. If volume remains, additional testing relevant to the pathogenesis of EVD or effects of the study treatment will be performed. Residual cells or buffy coat and plasma supernatant buffy coat may be retained for host genetic studies to identify susceptibility and severity markers.

